## Research Programme

Our research programme, Te Oranga Pūkahukahu (The Lung Health Check) aims to provide directly policy relevant information to guide the implementation of lung cancer screening nationally. The research programme is intentionally designed for Māori, aiming to reduce Māori mortality, and the life expectancy gap, from lung cancer.

To date the programme has focussed on three key pieces of work:

1. A survey alongside a series of focus groups to address important gaps in our understanding about how Māori would like to engage with a screening programme for lung cancer, and how the programme should be designed to reduce inequities. These findings have been incorporated into the design of this trial and a paper is currently in preparation.
2. A re-analysis of the cost effectiveness of lung cancer screening in NZ to address issues in a 2018 study from Jaine et al^44^ which concluded that LCS was unlikely to be cost-effective for any group in New Zealand. Jaine et al’s conclusions hampered progress in national discussions on lung cancer screening. Furthermore, more up-to-date data for some parameters in the model were available and the original authors did not undertake any equity-focused analyses. As a result of these issues, we undertook to update the cost-effectiveness modelling, using the original model. Our re-analysis found a number of issues with the model which altered the findings of the original study. Once these issues were corrected, we updated a range of parameters with the most recently available evidence and extended the model with alternative assumptions based on Māori health equity. Our resulting paper demonstrated that lung cancer screening is likely to be highly cost-effective for all populations groups, particularly for Māori women^45^.
3. Trialling lung cancer screening in New Zealand, initially Māori-specific.

## Aims and objectives

This study will focus on testing core invitation methods:

- a primary care practice based invitation and risk assessment process
- a DHB based centralised invitation and risk assessment process.

In this trial, we hypothesise that the invitation to lung screening conducted in primary care will result in higher levels of participation by Māori than a central hub with established expertise in conducting screening programmes and skills in active follow-up of Māori. This study is focused on:

- Determining the effectiveness of two lung cancer screening invitation strategies; primary care vs central hub
- Describing key lung cancer screening parameters to inform a potential national programme in NZ
- Testing the performance of the risk prediction tool
- Evaluating contextual implementation factors in order to optimise a future NZ screening programme, including incorporating COPD assessment

This is a Māori-specific study. It is the intention that, by identifying the most successful invitation methods for Māori, a successful screening program can be built which will allow detection of curable lung cancer. This in turn will reduce mortality, improve chances of cure, and substantially reduce health care costs in New Zealand. Current adult cancer screening programmes fail to deliver equitable outcomes for Māori. In order to avoid a LCS programme having similar inequitable outcomes we must design the programme so that it works well for Māori in the first instance.

In addition to the overall aims, we intend to test some of the key assumptions used in the sample size calculations and to test the planned processes.

Key questions that we will address include:

### Pilot phase

For the first group, trial participants will include DHB kaumatua, Te Hā Kotahi members and their whānau, and up to four primary care practices. This phase of the study will result in up to 50 scans, and will test key trial processes, including:

- Usability of the risk assessment tool
- Data collection and IT system
- Invitation materials
- Consent processes
- Results management
  - Reporting in private community radiology clinic
  - Standardised screen read and reporting
  - Use of volumetric analysis
  - Incorporation of blood biomarker analysis
  - Interpretation of results by providers and experience of providing results to participants and whānau
  - Interface between primary and hospital care for positive screen management

### Full trial

#### Primary outcome:

The full trial including a further 500 scans of eligible participants will address the primary research question of whether an invitation to lung screening conducted in primary care results in higher levels of participation by Māori than a central hub-based invitation method.

#### Secondary outcomes:

In addition, the trial will include the assessment of outcomes needed for the development of a national screening programme, including:

Participants and whānau experience of LCS:

- What is the participant and provider experience of LCS?
- What is the experience and acceptability of the shared decision making and results management processes as outlined in the protocol?
- What is the participant burden using the tools outlined in the study methods?
- What is the provider burden using the processes outlined in the GP clinic based arm of the study?

Parameters relating to recruitment and participation in the LCS pathway:

- What is the accuracy of recording of smoking history in general practice among those who are identified as potentially eligible for risk assessment i.e. those who are not recorded as ‘never smokers’?
- What % of Māori aged 55-74 in a general practice are potentially eligible for lung cancer screening
- What % of potentially eligible people agree to undergo risk assessment
- What % of those undergoing risk assessment are eligible for lung cancer screening
- What % of those eligible for lung cancer screening decide to proceed with screening
- What % of those who decide to proceed with screening attend their appointment for screening
- We have also included in our risk assessment a question about work place related exposure risks for lung cancer. The data from this question will contribute to a wider NZ study of lung cancer related to work place exposure.
- In addition, we will also ask participants about their lifetime exposure to passive smoking, using questions taken from the Lung Health Questionnaire developed for the International Lung Screening Trial (ILST). This data is collected using a standard validated scale, used in ILST and European trials, and will contribute to a future planned study of the relevance of the PLCO_M2012_ to the NZ population and how we can develop a more accurate risk model, particularly for Māori.

Parameters relating to the assessment of COPD within LCS:

- What is the prevalence of COPD among participants who proceed to CT scanning
- What are the characteristics of COPD in those assessed and diagnosed
- How are participants with COPD managed within primary care following this assessment
- How do GPs change the way they manage COPD after they are provided with COPD results and management recommendations
- What is the participant experience of COPD assessment
- How do participants view the inclusion of COPD assessment in future LCS programmes

## Study Design

A cluster randomised trial of two invitation methods to participate in LCS. The two invitation pathways will be tested end to end (invitation, risk assessment, shared decision making and CT scan).

Participating practices will be randomised (1:1) to either the primary care led or central hub arm. The randomization sequence is computer generated at the start of the study using a random number generation formula. For each pair of practices recruited, a sealed envelope containing an instruction that either the first or the second in the pair is to be placed in the primary care-led arm is opened by the programme manager. There are equal numbers of envelopes with each instruction and the envelopes are randomly sorted). Pairwise randomization ensures that there are equal numbers of practices in each group and it means that not all practices need to be recruited from the outset, a distinct advantage when recruiting primary care practices in the current, Covid-constrained environment.

Within the overall randomised trial of lung cancer screening methods will be a nested cohort study. In this sub-study, participants (those eligible for a CT scan) will be assessed for COPD.

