### Study setting/Location

The project will be hosted at Waitematā District Health Board (WDHB) and Auckland District Health Board (ADHB), in both primary care and hospital based facilities. We anticipate that we will initially recruit between 2 and 6 primary care practices in order to test key assumptions prior to continuing the study in the full cohort of up to a further 48 practices (24 in each study arm) (Figure 2). The CT scans will be conducted in private community fixed-site radiology facilities located centrally.

[figure not shown]

Figure 2: Practice Randomisation schematic (the groups will extend until we reach the required number of practices – up to a maximum of 48 (excluding pilot practices))

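### The equal-count envelope rule makes later practice allocations partly guessable and adds nothing to arm balance, which the pairing already guarantees

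*Protocol*

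**What the plan says.** All of the allocation procedure is in Protocol, Study Design. It opens with sequence generation: "The randomization sequence is computer generated at the start of the study using a random number generation formula". It then gives the unit and the instruction. One envelope is used per recruited pair, and it states that "either the first or the second in the pair is to be placed in the primary care-led arm". The envelope "is opened by the programme manager". The composition of the set is fixed: "There are equal numbers of envelopes with each instruction and the envelopes are randomly sorted".

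The same paragraph explains where equal arm sizes come from: "Pairwise randomization ensures that there are equal numbers of practices in each group". It adds, as an advantage, that practices need not all be recruited at the start, so pairs enter over time.

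Protocol, Study setting/Location, sets the size of the full trial at "up to a maximum of 48 (excluding pilot practices", with 24 practices per arm. That is at most 24 pairs.

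The protocol does not state how many envelopes there are, how 'first' and 'second' are assigned within a pair, or whether that order is recorded before opening. It describes no masking. Under Invitation to participate, the two arms differ visibly in who contacts people: clinic staff in one, hub staff in the other.

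**The concern.** A shuffled set with a fixed equal count is drawn without replacement. Each opening therefore carries information about those still to come. Allocation cannot be hidden once a practice starts inviting people, so staff who follow the trial can keep the tally.

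A restriction of this kind is normally accepted because it keeps the arms equal in size. Here it does not: each pair contributes one practice to each arm whichever instruction is drawn. The restriction costs some predictability and gives no arm balance in return.

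Predictability matters only if it can be used. The opening is the absence of a rule for 'first'. Someone who expects a particular instruction could influence which practice of a pair is listed first, or which practices are approached and in what order. At most 24 draws separate the arms, and Aims and objectives states the hypothesis in one direction, in favour of primary care. Placing a keener practice in one arm more often than chance would create a baseline difference that pairing does not remove.

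**Working it through.** **1. The plan's own number of practices.** Inputs from Table 4: uptake 40% and 50% (difference d = 0.10), ICC 0.03, m = 24 eligible patients per practice, variance reductions of 10% (individual) and 20% (group), power 80%, type I error 5%. The protocol cites its formula without printing it. A standard group-randomised form is

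g = (1.96 + 0.8416)² × V × [0.9 × (1 − 0.03) + 24 × 0.8 × 0.03] / (24 × 0.10²).

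The bracket is 0.873 + 0.576 = 1.449. With V = 0.49 (unpooled), 0.495 (pooled) or 0.50, g = 23.2, 23.5 or 23.7, which rounds up to 24 per arm. Multiplying g by 2 arms × 24 patients gives 1115 to 1137 eligible people, against 1134 in the Synopsis. The stated 24 per arm is reproduced with a two-sided 5% test; a one-sided test would give 19.

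**2. Arm balance.** Each of 24 pairs places one practice in each arm, so the arms are 24 and 24 for any sequence of instructions. The equal-count rule plays no part.

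**3. Predictability if the whole set is used.** Assume one envelope per pair at the maximum, so 2n = 24 and n = 12. A guesser who always names the instruction with more envelopes remaining expects

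n + ½ × (4ⁿ / C(2n, n) − 1) = 12 + ½ × (16,777,216 / 2,704,156 − 1) = 12 + 2.60 = 14.6 correct of 24, or 60.8%.

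Independent 50:50 draws give 12 of 24, or 50%. The expected number of envelopes at the end whose content is certain is 2n/(n + 1) = 24/13 = 1.85.

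**4. Other set sizes, all used.** The same formula gives 68.3% correct for 6 envelopes, 64.3% for 12, 62.2% for 18 and 59.9% for 30.

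**5. Stopping before a 24-envelope set is used up** (100,000 simulated orderings):

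| Pairs allocated | Correct guesses | Chance that any opened envelope was certain |
|---|---|---|
| 12 | 54.4% | 0% |
| 20 | 57.3% | about 4% |
| 22 | 58.5% | about 22% |
| 24 | 60.8% | 100% |

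**6. Upper bound on bias.** Take uptake of 45% (midway between the arms) and the plan's ICC.
- Between-practice SD = √(0.03 × 0.45 × 0.55) = 0.086.
- Expected gap between the better and worse of two practices = 2 × 0.086 / √π = 0.097.
- If the better practice is always recognised and listed according to the guess, bias = 0.097 × (2 × 0.608 − 1) = 0.021. With the plan's 20% group-level variance reduction it is 0.019.
- The standard error implied by 80% power for 10 points is 0.10 / 2.80 = 0.0357, so the shift is 0.53 to 0.59 standard errors. Two-sided type I error becomes about 8.2% to 9.1% instead of 5%.
- With stopping at 20 or 12 pairs the same bound on bias falls to about 1.4 points (0.097 × 0.146) or 0.85 points (0.097 × 0.088).

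**The case against.** **Timing limits misuse.** The wording "For each pair of practices recruited, a sealed envelope containing an instruction" suggests that both practices are already in when the envelope is opened, and 'first' most naturally means first to be recruited. On that reading, steering needs influence over sign-up order, guided by an imperfect guess. This stands and reduces the practical risk. It does not remove it, because the reading is not written down and the recruiting team can affect the order in which practices sign up.

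**The set may never be exhausted.** A reader might infer that the last allocations are always known. The protocol does not support that: the set size is not given, 48 practices is a ceiling, and numbers may be adjusted to reach the scan target. Certainty is rare if recruitment stops even a few pairs short.

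**The bias figures are not expected effects.** A reader might take 2 points, or a type I error of 8% to 9%, as what this design will produce. Those figures need full use of the set, perfect recognition of the better practice and control of the order in every pair. Nothing in the protocol shows that any of this happens. Motive is also not one-sided: Secondary research questions traces the question to a survey finding of equipoise between the strategies.

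**Three further inferences are unsupported.** That the recruiting team keeps the envelopes does not follow from who opens them; custody is not described. That sealed envelopes could be read in advance has no basis in the text and is unrelated to the equal count. That the computer-generated sequence and the envelopes are competing mechanisms is also not established, because the envelopes can simply be how that sequence is carried out.

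**Equal counts may balance joining order.** If 'first' means earlier to join, equal counts ensure that earlier-joining practices are spread evenly over the arms. With independent draws over 24 pairs, a split of 14:10 or worse occurs about 54% of the time. This is a real but minor cost, and the protocol does not give it as the reason for the rule.

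**Conclusion.** The point holds as an avoidable weakness in allocation concealment. The equal-count rule contributes nothing to arm balance and raises the chance of a correct guess above the 50% of independent draws: about 61% with 24 envelopes all used, about 57% if recruitment stops at 20 pairs and about 54% at 12. These figures rest on an assumed 24 envelopes and on a guesser who has seen every earlier opening. That earlier openings become known is inferred from the visibly different arms, because the protocol does not call the trial open.

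A bias of about 2 points of the 10-point target is a ceiling, not an estimate, and the protocol gives no evidence of steering. The change is still worth making, because the restriction has no stated benefit and removing it costs almost nothing.

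**What to change.** In Protocol, Study Design, replace the equal-numbers rule with an independent 50:50 computer-generated draw for each pair. State that a pair's allocation is revealed only after both practices and their first/second order have been logged with a date. Fix the order by a stated rule, for example the date of signed agreement. State that the list is kept from those who recruit practices.

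Pairs already allocated keep their assignment; the new procedure applies to the remaining pairs.

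The cost is one paragraph of protocol text and a short allocation log. Arm sizes remain equal through the pairing, and the sample size and power are unchanged. The small downside is that 'first' and 'second' instructions, and so joining order within pairs, may be unequal between the arms by chance.

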### Study setting/Location

The project will be hosted at Waitematā District Health Board (WDHB) and Auckland District Health Board (ADHB), in both primary care and hospital based facilities. We anticipate that we will initially recruit between 2 and 6 primary care practices in order to test key assumptions prior to continuing the study in the full cohort of up to a further 48 practices (24 in each study arm) (Figure 2). The CT scans will be conducted in private community fixed-site radiology facilities located centrally.

[figure not shown]

Figure 2: Practice Randomisation schematic (the groups will extend until we reach the required number of practices – up to a maximum of 48 (excluding pilot practices))

### Study Population

The initial study population includes all Māori between the ages of 55 and 74 who are not recorded as “never smokers” in the practice management system.

### Eligibility Criteria

#### Patient eligibility criteria:

- Recorded as Māori in the primary care enrolment
- Enrolled in participating general practices
- Able to provide informed consent to participate
- Agree to undergo the activities required for participation in the trial

#### Patient exclusion criteria:

- Never-smokers
- Previous diagnosis of lung cancer
- Have other non-curatively treated cancer outside the lung
- Clinical symptoms suspicious for lung cancer e.g. haemoptysis, chest pain, and weight loss
- Have received chemotherapy or cytotoxic drugs within the last 6 months
- Documentation of a chest CT within two years (this will be initially checked by asking the participant if they have had such a scan, followed by a review of records to confirm)
- Pregnancy
- Unable to provide informed consent due to cognitive problems
- Unwilling to provide consent
- Additionally, for the assessment of COPD, if participants are unwilling or unable (due to a comorbid disease) to undergo spirometry testing they will be excluded from this part of the study.

### Deferrals

- Pneumonia or bronchitis requiring antibiotic treatment within the last 12 weeks

### Study Procedures/Methods

The overall study schematic is outlined in Figure 3.

### Recruitment of participants

#### Identification of potentially eligible participants

Permission will be requested from PHOs to access primary care enrolment data initially. The PHOs of practices who agree to participate in the study will compile lists of potentially eligible Māori, aged 55-74 who are not recorded as “never smokers”. We will request a waiver of consent from HDEC to allow access to these data.

Participating practices will conduct an initial review of the potentially eligible participant list and assess for inclusion and exclusion criteria and refine the initial list.

Practices will provide the study team with the finalised lists that include demographic information, contact details, relevant medical history, and recorded smoking status including all excluded participants with reasons for exclusion.

#### Randomisation of practices

General practices will be randomised at a 1:1 ratio to either the primary care or centralised arm of the trial. This will reduce the risk of contamination if patients were the unit of randomisation and patients in both arms of the trial were located in the same practice.

[figure not shown]

Figure 3: Study schematic

#### Invitation to participate

Potentially eligible people will be sent an email, letter or text with a link to study information, advising them that they will be contacted about participating in the trial and COPD assessment, including an overview brochure and a participant information sheet outlining the risk assessment process. For participants in the central hub arm, this will include a phone number they can use to contact the central hub to request further information, decline participation, or proactively begin participation. Participants in the GP arm, will be advised to contact their GP regarding any possible questions. They may opt out of any further contact if they wish at this point.

After a 10 to 14-day period participants will be contacted by phone and invited to participate in the trial by a nurse or other clinic staff (GP clinic arm), or by a staff member of the central hub (see Figure 3). Five attempts to contact potentially eligible participants from the list will be made, thorough a variety of methods (email, phone, letter, text). In both arms, phone calls and texts will be made at different times of day (e.g. daytime and evenings). Based on our prior equity-focused research we have found additional contact attempts were important to support participation in the studies. Contact attempts will be captured in the study IT system. Declining to participate will result in no further contact about this study.

The purpose of the contact is to explain the trial, if interested, and then to confirm inclusion/exclusion criteria. For eligible participants, we will then seek verbal consent to participate in the risk assessment. Potential participants will be sent the full Risk Assessment Participant Information Sheet, and will be given sufficient time to read it and ask questions.

In the primary care-based arm clinic staff will undertake this process. Primary care arm staff will also be able to engage with people on the list opportunistically, if they attend the practice for another reason.

In both arms, staff involved in this invitation procedure will be given training and a procedure manual to ensure that trial procedures are standardised.

#### Whānau involvement

Whānau or other support people are both invited and welcomed to participate in all of the parts of the lung cancer screening processes and COPD assessment – from invitation, risk assessment, shared decision making, CT scan through to management of results.

#### Risk Assessment for Prediction of Lung Cancer Risk

The risk assessment will be done by practice nurses (primary care arm) or the project research nurse (central arm) in-person or over the phone depending on patient preference. A standardised protocol for completing the risk assessment will be used; staff in both arms of the trial will receive training in this and a procedure manual will be provided to everyone undertaking these assessments. Whānau or other support people can participate in the risk assessment process.

The PLCO_M2012_ risk prediction tool will be used to assess a participant’s risk of lung cancer. Participants with a $\geq2 \%$ risk of developing lung cancer within six years will be eligible for a CT scan.

People with a ≥30 pack-years smoking history will be eligible for lung screening even if their PLCO_M2012_ derived risk is below the 2% threshold. Pack-year is defined as number of packs of cigarettes smoked per day multiplied by the number of years smoked. If a participant stopped smoking for 6 months or more and then restarted smoking again, the time will be subtracted from the total duration of smoking in 0.5-year increments.

